## 2. Materials and Methods

### 2.1. Design

The ExIC-FEp study will be a single-blind, three-arm RCT to analyze two types of supervised physical exercise in participants with HFpEF for 6 months. Additionally, this protocol for RCT has been registered for clinical trials (NCT05726474).

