### 2.5. Intervention

#### 2.5.1. Training Interventions

Participants in groups 1 and 2 will perform supervised intensity training on an ergometer bicycle. Exercise intensity (relative to maximum heart rate (HRmax) and maximum heart rate percentage (%HRmax) will be determined by a maximal cardiopulmonary stress test at baseline. 

**CE** (Group 1). Participants will exercise for 40 min three times a week on an ergometer bike at 50–60% of VO2max, 60–70% of HRmax and 11–13 on the Borg scale, without respiratory distress. In addition, strength training (bench press, leg press, leg curl, rowing machine, triceps dip, pec pull) will be performed twice a week. The strength training will be performed with 15 repetitions per exercise per session, with a workload corresponding to 60% to 65% of the 1 repetition maximum (1RM) measured at the beginning and end of the intervention.

**HIIT** (Group 2). Participants will perform three training sessions per week. Each training session will begin with a 10-min warm-up at moderate intensity (corresponding to 50–60% of VO2max, 60–70% of HRmax, and 11–13 on the Borg scale, without respiratory distress) before four 4-min intervals at high intensity (corresponding to 85–90% of VO2max, 90–95% of HRmax, and 15–17 on the Borg scale, with mild respiratory distress). Each interval will be separated by 3 min of active pauses, with an HRmax of 50–70%. The training session will end with 3 min of cool down at moderate intensity (corresponding to 50–60% of VO2max, 60–70% of HRmax, and 11–13 on the Borg scale, without respiratory distress). The total exercise time will be 40 min for the HIIT group. 

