#### 2.5.2. Control Group (Group 3)

CG participants will receive standard advice on the general cardiovascular benefits of physical exercise according to current guidelines (30 min of walking on most days of the week) [35] and will continue their usual daily leisure-time physical activity throughout the study.

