### 2.7. Outcomes

#### 2.7.1. Primary Outcomes

*Exercise capacity by maximal cardiopulmonary exercise test with Ergoline600 ergometer bicycle:*
−Gas analyzer (K5 COSMED): VO2max, ventilation slope/carbon dioxide production (VE/VCO2) per minute, and ventilatory threshold (VT).−Workload measured in watts.−Average exercise time in minutes.−HRmax by Polar H10 heart rate monitor.−A 6-min walking test, in a 30-m corridor, to be performed by walking from one side to the other along this stretch of corridor, which will be delimited by cone-type indicators. These signs will be placed 29 m from each other, leaving 0.5 m at each end for the subject to turn. The test will be performed accompanied by the examiner. The primary test outcome is the final distance walked.

*Echocardiography:*
−Using Sonosite SII Doppler ultrasound (Sonosite Inc., Bothell, WA, USA), the following will be measured: E velocity (m/s), A velocity (m/s), E/A ratio, e’ velocity (m/s), E/e’ ratio, ejection fraction percentage, left ventricular volume index, end-diastolic volume, left ventricular mass, left atrial diameter, isovolume relaxation time, deceleration time (m/s) and left atrial volume index.

*Endothelial function:*
−Carotid intima-media thickness (cIMT): by ultrasound with the Sonosite SII device (Sonosite Inc., Bothell, WA, USA).

*Arterial stiffness:*
−Pulse wave velocity (PWv) and central augmentation index (cAIx) using the Mobil-O-Graph PWA (I.E.M. GmbH, Stolberg, Germany).

*Quality of life:*
−Validated 12-item health questionnaire (SF-12).−Validated Minnesota Living with Heart Failure Questionnaire (MLWHFQ).

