### 2.9. Sample Size Calculation

The sample size calculation is based on data from the RCT by Mueller et al. [31] which reveals that 21 participants per group would provide 80% power at *p* < 0.05 to detect a statistically significant result for VO2max, the primary outcome. Considering the three groups (CE, HIIT and GC) and a dropout rate of 20%, a total of 72 participants will be recruited.

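### The six-minute walk is performed with the examiner accompanying the participant, which lets the examiner influence pace; one sentence should be reworded to rule that out

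*Protocol article*

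**What the plan says.** The protocol article, section 2.7.1 (Primary Outcomes), places the walk in the exercise-capacity block and describes it in some detail: "A 6-min walking test, in a 30-m corridor, to be performed by walking from one side to the other along this stretch of corridor". It gives the cone spacing and the turning allowance at each end. It then fixes the examiner's part, "The test will be performed accompanied by the examiner", and the endpoint, "The primary test outcome is the final distance walked". It sets no walking speed and does not say where the examiner is to be relative to the participant.

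On blinding, section 2.1 says "The ExIC-FEp study will be a single-blind, three-arm RCT". Neither that section nor any other says who is blinded.

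On what participants know, section 2.5.1 says "Participants in groups 1 and 2 will perform supervised intensity training on an ergometer bicycle", and section 2.5.2 says "CG participants will receive standard advice on the general cardiovascular benefits of physical exercise according to current guidelines".

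On the weight of the walk within the trial, section 2.9 bases the sample size on a different measure: "21 participants per group would provide 80% power at *p* < 0.05 to detect a statistically significant result for VO2max, the primary outcome".

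**The concern.** Nothing in the description prescribes a speed, so the pace is the participant's to choose, and the distance is that pace multiplied by six minutes. If the examiner walks beside or ahead, the participant may match the examiner's speed, and the distance then partly measures the examiner.

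Two consequences are possible. If the influence varies from walk to walk without relation to the arm, it adds noise to a small trial. If it differs by arm, it biases the comparison. The second needs an examiner who knows or guesses the allocation. Participants know whether they trained under supervision or only received advice, and a walk done together gives them an opportunity to reveal it at the moment when the examiner can affect the result.

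What is at stake is the quality of one listed primary outcome. It is the only measure in the exercise-capacity block that does not belong to the bicycle test, and both training arms train on a bicycle.

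**Working it through.** The plan states no figure on this point, so there is none to reproduce. The check has two parts.

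**Reading the text**

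1. The walk is a listed primary outcome and its result is the final distance (section 2.7.1).
2. The test consists of walking up and down a corridor. For a test of that kind, the plain meaning of *accompanied* is that the examiner goes along.
3. No sentence limits the examiner's position or pace.
4. Participants cannot be blinded, because the arms differ visibly (sections 2.5.1 and 2.5.2). The single-blind label therefore most naturally covers someone on the study side, but the article does not say whether that is the walk examiner.
5. The ANCOVA in section 2.10 adjusts for the baseline value. That does not remove an influence that acts at follow-up and differs by arm.

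**Scale, under assumptions only**

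The documents give no walk distance, no standard deviation (SD) and no size for any examiner effect. Every input below except the group size, the significance level and the use of Bonferroni is an assumption.

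*Pace to distance.* Distance = pace × time, so a given percentage change in pace gives the same percentage change in distance. For an assumed walk of 350 to 450 m and an assumed pace change of 3 to 5%:
- low end: 350 m × 0.03 = 10.5 m
- high end: 450 m × 0.05 = 22.5 m

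*Noise.* Suppose pacing adds independent variation with an SD equal to k times the SD otherwise present. The variance is then multiplied by 1 + k²:
- k = 0.2: 1 + 0.04 = 1.04
- k = 0.3: 1 + 0.09 = 1.09
- k = 0.5: 1 + 0.25 = 1.25

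*Bias.* Suppose there is no true difference between two arms, but the examiner shifts one of them by b SD. For a two-sample t-test with n = 21 per group (section 2.9), the degrees of freedom are 2 × 21 − 2 = 40 and the noncentrality is b × √(n/2) = b × √10.5 = 3.24b. The two-sided rejection rates from the noncentral t distribution are:

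| Assumed shift b (SD) | Level 0.05 | Level 0.05/3 = 0.0167 |
|---|---|---|
| 0.1 | 6.2% | 2.2% |
| 0.2 | 9.7% | 4.0% |
| 0.3 | 15.8% | 7.3% |
| 0.5 | 35.3% | 20.3% |

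The right-hand column applies the Bonferroni correction of section 2.10 to the three pairs of arms. The result depends little on the exact group size: at b = 0.2 and level 0.05 it is 9.2% with 19 per group and 10.4% with 24 per group (72/3). The table shows what a given arm-related shift would do. It is no evidence that such a shift would occur.

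**The case against.** The strongest reply is that everything turns on one word. *Accompanied* can mean that the examiner is present throughout, or walks behind; the article nowhere says that the examiner walks beside or ahead or sets the pace. This stands as a limit on certainty. It does not remove the point: the article specifies the walk down to the cone spacing and chose to fix the examiner's role in these terms, so if mere presence is meant, the sentence still needs rewording.

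A second reply is that a journal article leaves test-manual detail elsewhere. That holds for scripted encouragement and for the separation of testers from trainers, and neither is requested here. It does not cover a procedure that the article states.

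Third, an influence that is the same in all arms and visits largely cancels in between-arm differences. That also holds, and leaves only variable or arm-related pacing as a problem.

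Fourth, a reader might infer that the walk result will be biased towards exercise. The documents do not support this. It would take both an examiner aware of the arm and pacing that differs by arm, and neither is documented; the single-blind label may well cover the examiner. Participants could also disclose their arm in any other test, so disclosure as such is not peculiar to the walk.

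Finally, a reader might treat the walk as the trial's main check on carry-over to daily life. Sections 2.7.1 and 2.7.2 also include two quality-of-life questionnaires, nine-day accelerometry and step counts, so that would overstate its place.

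**Conclusion.** The point holds as a cheap improvement to how one listed primary outcome is measured. On the plain reading, the stated procedure allows the examiner to influence the pace of a test whose result is distance. This can add noise, and it can add bias if the examiner knows or guesses the arm, which the article does not exclude.

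The size cannot be derived from the documents. The metre figures, variance factors and false-positive rates above are illustrations from assumed inputs and should not be quoted as estimates of harm. It would also go too far to conclude that the trial's main result is at risk: section 2.9 sizes the trial on VO2max, and the sentence at issue concerns only the walk.

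The conclusion rests on reading *accompanied* as going along with the participant. If the full protocol already keeps the examiner at a fixed point or behind the participant, only the wording of the article needs to change.

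**What to change.** Replace the accompaniment sentence in section 2.7.1 with one that says three things:

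- The examiner does not walk beside or ahead of the participant, but observes from a fixed point in the corridor.
- Where the site judges accompaniment necessary, the examiner follows behind without setting the pace.
- The same procedure is used in all arms and at all visits.

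This changes one sentence and leaves the equipment, sample size and analysis as they are. The downside is slightly less close observation during the walk, which the option of following behind limits.

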#### 2.7.2. Covariables

*Sociodemographic variables:*
−Age.−Sex.−Socioeconomic level: using the Spanish Society of Epidemiology scale. Participants will report their educational level and employment status, and an index will be calculated considering both.

*Patient medical history:*
−Comorbidities (hypertension, diabetes, smoking, alcohol consumption).−Pharmacological treatment.

*Anthropometric variables:*
−Weight: mean of two weight measurements (Seca^®^ 861 scale), with the participant barefoot and lightly wrapped.−Height: mean of two measurements with a wall-mounted measuring rod (Seca^®^ 222), with the participant barefoot, in an upright position and with his/her sagittal midline coinciding with the measuring rod.−Body mass index: body mass index will be calculated by the formula weight (kg)/height^2^ (m^2^).−Waist circumference: mean of two measurements of waist circumference with a flexible tape measure at the midpoint between the last rib and the iliac crest at the end of a normal exhalation.−Body fat percentage: mean of two measurements from an 8-electrode electrical bioimpedance model Tanita^®^ BC-418 MA (Tanita Corp., Tokyo, Japan).−Densitometry (DXA) (model GE-Lunar DXA): densitometry will be performed to estimate fat mass, lean mass and bone mineral density.−Blood pressure: mean of two blood pressure determinations separated by a 5-min interval. The first measurement is obtained after a rest of at least 5 min. The subject is seated in a quiet environment, with the right arm semi-flexed at heart level. Blood pressure will be measured with the Omron^®^ M5-I monitor (Omron Healthcare UK Ltd., Milton Keynes, UK) and cuffs of three sizes according to arm circumference.

*Muscle strength:*
−The manual grip strength will be determined with the TKK 5401 Grip-D dynamometer (Takey^®^, Tokyo, Japan).

*Spirometry (Datospir Touch Easy-T):*
−Forced vital capacity (FVC).−Forced expiratory volume in the first second (FEV1).−FEV1/FVC ratio.

*Biochemical parameters:*

Blood will be drawn from a vein in the antecubital fossa between 8:15 and 9:00 a.m., after at least 12 h of fasting.

The following will be determined:
−Glucose, total cholesterol, triglycerides, HDL cholesterol, LDL cholesterol, apolipoproteins A1 and B, insulin and ultrasensitive C-reactive protein. The determinations will be made on a Roche Diagnostics^®^ Cobas 8000 system, and the insulin determination will be made on the Abbott^®^ Architect platform.−N-terminal pro-B-type natriuretic peptide (NT-proBNP). Plasma concentrations of NTproBMP will be determined by enzyme-linked immunosorbent assay (ELISA) (R & D Systems, Minneapolis, MN, USA).−HbA1c will be determined by high-performance liquid chromatography on an ADAMS A1c HA-8180 V analyzer from A. Menarini Diagnostics^®^, a method certified by the National Glycohemoglobin Standard Glycohemoglobin Standardization Program (NGSP) and the International Federation of Clinical Chemistry and Laboratory Medicine (IFCC).

*Physical activity:*
−Accelerometry: Physical activity will be objectively measured using AX6 accelerometers (Axivity) for nine consecutive days (including nights).−Podometry measured by using the Xiaomi MI Band 3 smart bracelet. This device will also be used to provide information during the study on sleep time and sedentary time.

*Mediterranean diet adherence:*
−Validated 14-item Mediterranean diet adherence questionnaire (MEDAS-14).

The basic clinical features are shown in Table S1.

### 2.8. Ethical Considerations

This study protocol has been approved by the Clinical Research Ethics Committee of the Hospital Virgen de la Luz in the city of Cuenca where the study is to be performed (REG: 2022/PI2122).

Participants will be informed of the objectives and methods of the study and will be asked to confirm in writing their approval to participate in the project.

### 2.9. Sample Size Calculation

The sample size calculation is based on data from the RCT by Mueller et al. [31] which reveals that 21 participants per group would provide 80% power at *p* < 0.05 to detect a statistically significant result for VO2max, the primary outcome. Considering the three groups (CE, HIIT and GC) and a dropout rate of 20%, a total of 72 participants will be recruited.

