### 2.4. Randomization

After informed consent and screening, participants will be randomly distributed (1:1:1) using EPIDAT 4.2 software (Figure 1) into three groups: group 1, CE (continuous aerobic exercise with moderate intensity strength exercises); group 2, HIIT; and group 3, control group (CG).

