### 2.10. Statistical Analysis

The statistical analysis will consist of three phases. The first will consist of testing the effectiveness of randomization in creating three comparable groups of participants with HFpEF, exploring the presence of outliers, and testing the degree of adjustment of the main variables to the normal distribution.

In the second phase, ANCOVA models will be used (baseline and 3 months) in which the dependent variables will be each outcome variable, and the intervention will be the fixed effect (2 = CE, 1 = HIIT and 0 = GC), adjusted for baseline, age, sex and socioeconomic status. The results will be expressed as absolute differences in changes in variables between baseline and final measurements (95% confidence interval (95% CI)). Bonferroni post hoc tests will be performed for paired comparisons.

In the third phase, a comparison of CE, HIIT and CG will be performed using the propensity score matching method to take into account covariate imbalance in baseline measurements between subjects. The propensity score estimates the effect of the intervention using a causal inference model, which explains what would have happened if all subjects in the intervention and control groups had the same characteristics at baseline. Each subject is matched to a subject with similar characteristics using a 0.40 caliper using the psmatch2 command.

All analyses will be performed by INTENT TO TREAT, keeping subjects in the originally assigned intervention or control group, regardless of the number of physical activity program sessions attended, and considering the CONSORT.

The results with *p* < 0.05 will be considered statistically significant. The analysis will be performed with the STATA16 statistical package. 

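### Recruiting 72 does not leave 21 per group after 20% dropout, so the stated 80% power is not delivered

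*Protocol article*

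**What the plan says.** Section 2.9 (Sample Size Calculation) of the protocol article takes its requirement from a published exercise trial: "21 participants per group would provide 80% power at" the 0.05 level, "to detect a statistically significant result for VO2max, the primary outcome". It then moves from the requirement to the recruitment target in one step: "Considering the three groups (CE, HIIT and GC) and a dropout rate of 20%, a total of 72 participants will be recruited".

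Section 2.4 (Randomization) fixes equal allocation: "participants will be randomly distributed (1:1:1) using EPIDAT 4.2 software". A total of 72 is therefore 24 per arm.

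The section does not show how 72 was obtained from 21 per group. It gives no effect size, standard deviation or sidedness.

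**The concern.** The section prints a per-group requirement, a dropout rate and a recruitment total, and the first two should determine the third. They do not. If 20% of 72 participants provide no VO2max result, fewer than 21 per arm remain, and the 80% power attached to 21 per arm no longer applies.

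The trial recruits to this total, and readers will judge a null VO2max result against this power statement. On the plan's own dropout assumption, the stated power is too high.

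**Working it through.** **Inputs**

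| Input | Value | Source |
|---|---|---|
| Required per group | 21 | Section 2.9 |
| Power at that size | 80% | Section 2.9 |
| Significance level | 0.05 (two-sided assumed) | Sections 2.9 and 2.10 |
| Groups, allocation | 3, 1:1:1 | Sections 2.9 and 2.4 |
| Dropout | 20% | Section 2.9 |
| Recruitment total | 72 | Section 2.9 |
| Effect size, SD | not given | – |

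**Step 1: try to reproduce 72.** The evaluable total is 3 × 21 = 63.

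| Inflation | On the total | Per arm, then × 3 |
|---|---|---|
| Divide by (1 − 0.20) | 63/0.80 = 78.75, so 79 | 21/0.80 = 26.25, so 27; 81 in total |
| Multiply by 1.20 (a common mistake) | 63 × 1.20 = 75.6, so 76 | 21 × 1.20 = 25.2, so 26; 78 in total |

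None gives 72. The shortfall against the correct inflation is 79 − 72 = 7, or 81 − 72 = 9 with equal arms.

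**Step 2: what 72 leaves.**

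- After 20% dropout: 72 × 0.80 = 57.6 in total, or 57.6/3 = 19.2 per arm.
- Dropout at which exactly 63 remain: 1 − 63/72 = 0.125, or 12.5%.

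**Step 3: power at the retained size.** Because no effect size is printed, I solve for the one that makes 21 per group give exactly 80%, then hold it fixed and reduce the group size.

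*Normal approximation, two groups, two-sided 0.05.* The standardised difference is d = √(2/n) × (1.960 + 0.842). With n = 21, d = 0.865. Power is Φ(d√(n/2) − 1.960). At n = 19.2 this is Φ(2.679 − 1.960) = Φ(0.719) = 76.4%.

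The same back-solve was repeated under other readings of the 21:

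| Reading of the 21 per group | Implied effect | Power at 19 per arm | Power at 19.2 per arm |
|---|---|---|---|
| Two-sample, normal, two-sided | d = 0.865 | 76.0% | 76.4% |
| Two-sample, noncentral t, two-sided | d = 0.886 | 75.7% | 76.2% |
| Two-sample, normal, one-sided | solved the same way | 76.4% | 76.8% |
| Three-group omnibus, noncentral F | f = 0.401 | 75.4% | 75.9% |

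Every reading gives between 75.4% and 76.8%. These figures are at the unadjusted 0.05 level. Section 2.10 plans Bonferroni paired comparisons, but that is a separate matter and adds nothing to the shortfall counted here.

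**The case against.** The arithmetic in steps 1 and 2 is not disputed. The objections concern what follows from it.

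- **The 76% is conditional.** Without an effect size or SD, the power at 19 per arm rests on taking the plan's 21 and 80% at face value. This stands. The headcount mismatch does not depend on it, and the loss is much the same under every test tried.
- **The baseline-adjusted ANCOVA could recover the loss.** If the 21 came from an unadjusted comparison of final values, a baseline correlation of about 0.3 would offset it: 1 − r² = 19/21 gives r = 0.31. This is possible, but Section 2.9 claims no such gain, and how the 21 was derived is not shown.
- **The slip may lie in another figure.** 20 × 3 × 1.2 is exactly 72, and 63 × 1.15 = 72.45, so the error could be in the 21 or the 20%. This stands as an explanation but not as a defence: even 20 per group would need 60/0.80 = 75.
- **Intention to treat keeps everyone in the analysis.** Section 2.10 keeps participants in their assigned group whatever their attendance. That deals with adherence. It does not supply a missing VO2max value, and Section 2.9 itself treats dropout as a loss to be made up by recruitment.
- **The effect is small.** About 4 points of power and 2 participants per arm introduce no bias and do not change the type I error. That is a fair description of the size. The printed figures still contradict each other.

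**Conclusion.** The concern holds. With 21 per group, 20% dropout and 1:1:1 allocation, a target of 72 is too low by 7 participants, or 9 with equal arms. It leaves about 19 per arm and tolerates 12.5% dropout, not 20%. This rests only on figures printed in Sections 2.4 and 2.9.

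If 21 per group does give 80% power, power at the stated dropout is about 76%. That figure assumes the back-solved effect and that participants who drop out contribute no VO2max outcome. Whether 21 is itself right cannot be checked from the article.

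**What to change.** Restate Section 2.9 so that its figures agree. Either route works:

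1. **Keep 72.** State that 72 participants (24 per arm) give 80% power if dropout is no more than 12.5%, and about 76% if it is 20%.
2. **Keep 80% power and 20% dropout.** Change the total to 79, or to 81 for equal arms. With 27 per arm, 27 × 0.80 = 21.6 remain.

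Before choosing, the sponsor should check the 21 and the 20% against its own calculation. The 76% should be recomputed from the actual effect size and SD, since the value here is back-solved.

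The first route costs one sentence, enrols nobody extra, and makes the stated power or tolerated dropout slightly less favourable. The second costs 7 to 9 more participants.
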